## 7. Investigational Events

### 7.1 Endpoints

### **7.1.1 Primary**

The primary endpoint is:

- a) Self-Reported Saturated Fat Intake

### **7.1.2 Secondary**

The secondary endpoints are:

- a) Intervention effects on self-efficacy, risk perceptions, intention, outcome expectancies as measured by the Health Action Process Approach Model.

## **8. Experimental evaluations**

### **8.1 Biological Samples**

No biological samples are being collected in this study and there are no invasive measures.

## **9. Safety**

Subjects will be recruited only when the appropriate approvals have been granted.

### **9.1. Unilever Safety Clearance Requirements**

N/A

### **9.2. Local Research Ethical Review Requirement**

The authorised protocol and other appropriate documentation will be subject to the approval of Independent Ethics Committee in Colworth. The study will not proceed without the written approval of the Ethics Committee and any recommendations for change or additions will be discussed and necessary changes made. Finally the Research Ethics Committee will be sent a summary of the study findings for their information.

### **9.3. No Fault compensation**

In the unlikely event of any subject suffering any significant deterioration in health or wellbeing arising as a result of taking part in this study, Unilever has undertaken to compensate them without having to prove that anyone involved in this study has been negligent. Any dispute will be referred to an arbitrator.

### **9.4. Data Protection**

Information relating to this study will be kept confidential and the subjects' right to check personal data will be fully protected in accordance with the Data Protection Act 1998. Use of Case Record Forms is not applicable in this study since all information will be gathered via an online system. Each subject will be allocated with a unique ID at the recruitment stage (by Virtual Surveys) which will remain the same until the end of the study. Subjects will be responsible for entering their data on the system and no personal details such as (first name, last name and email addresses will be asked of the subjects). However, subjects will be required to fill out personal health information, gender, date of birth into the website in order to receive feedback at the end of the study.

The subject may choose not to provide certain information, but this may mean they will not be able to complete the study and their data will be replaced by new

participant data. The site will not contact the user and Unilever Corporate Research will not knowingly sell, rent, or trade the personal information collected.

All web-based interaction data will be stored for a period of five years in a secure central database hosted by Tessella Services on behalf of Unilever. Data files on the mainframe will be backed-up automatically. All data files will be backed-up and stored in a secure location.

## **9.5 COSHH**

N/A

## **9.6 Head of Research**

Once all of the study approvals have been collected, the Corporate Clearance form will be signed off by the Head of Corporate Research.

## **9.7 Microbiology**

N/A

## **10. Serious Adverse Events**

Any adverse event that is considered SERIOUS must be reported within one working day by the investigator to the sponsor/study co-ordinator (for definition see Protocol part III; section 2.5 “Adverse Event”).

## **11. Statistical Considerations**

### **11.1 Description of Statistical methods and interim analysis**

This is a randomised, stratified, between-groups study using a 2x2 factorial design with the factors 'use of the Heart-Age tool' and 'use of planning'. The primary endpoint is the change in saturated fat intake in participants allocated to the four different experimental conditions (Heart-Age and Planning, Heart-Age, Planning and Control Group). Participants will be randomly allocated to one of these four conditions, stratifying for age group (30-45 years or 46-60 years) and gender. Their saturated fat intake will be measured at baseline and the completion of the study (4 weeks after enrolment). The statistical analysis will compare the efficacy of the four treatment groups via the change in saturated fat intake between the baseline and final diet assessments. There will be no interim analyses.

### **11.2 Data Analysis and Plan of Efficacy**

A full statistical analysis plan will be formulated in collaboration with [name] from the Unilever Statistics Group, Colworth Park. The effect of the design factors will be determined by comparing the proportion of subjects who have reduced their saturated fat intake, using a logistic regression model which includes the two design factors and their interaction. Further analysis on the actual mean level of reduction may also be carried out, using an analysis of variance model including the design factors and their interaction (data transformations may be required to ensure normality assumptions are not violated). The stratification variables will be included in the models as will other covariates found significant at the 0.05 level. Comparisons between levels of a design factor will all be reported using two-sided significance

levels (i.e. making no prior assumption about which treatment group will be most effective).

If there are any relevant differences at baseline measurements between the four groups, we will adjust the outcome of these factors (e.g. diet knowledge, history of saturated fat intake, socio-economic status). Separate analysis of the effects of modifiers and mediators will be conducted in order to gain a better insight as to who benefits from the intervention.

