### Primary Outcome

#### Saturated Fat Intake

Self-reported amount of saturated fat intake will be measured by Margetts et al (1989) 63 item questionnaire and a two-item self-reported measure. The Margetts, Cade & Osmond (1989) questionnaire is a validated self-report index of food. The frequency of consumption of 63 common foods over the previous month using a 6-point-scale is assessed (two or more times per day; three to five times per week; one to three times per month; rarely or never). The scale has good test-retest reliability ( $r=.61$ ; Armitage & Conner, 1999).

Saturated fat intake will be also measured by a two item self perception questionnaire.

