### **11.3 Sample size and power determination**

The primary endpoint of saturated fat intake reduction will be assessed by calculating the proportion of subjects who reduced that intake within each of the four treatment groups and comparing these proportions. Comparisons between groups will then be based on 100 subjects per group. Comparisons between the factors (i.e. 'use of the Heart-Age tool' and 'use of planning') will be based on 200 subjects.

A sample size of 200 subjects per cell will allow a difference in proportions of correct responses of approximately 0.08 to be detected at a two-sided 0.05 significance level with power of 0.8, assuming that the lower proportion is around 10% of subjects (i.e. the 10% of non-Heart-Age users their saturated fat intake, then we would need 18% of Heart-Age users to reduce to have a good chance of detecting a significant difference).

A sample size of 100 subjects per cell will allow a difference in proportions of correct responses of approximately 0.12 to be detected at a two-sided 0.05 significance level with power of 0.8, assuming that the lower proportion is around 10% of subjects (i.e. the 10% of Heart-Age non-planners reduce their saturated fat intake, then we would need 22% of Heart-Age planners to reduce to have a good chance of detecting a significant difference).

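### The primary analysis cuts the change in saturated fat intake to reduced yes/no, which discards about a third of its information, and section 11.3 gives about 64% power, not 80%, even at its own 10% rate

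*Protocol*

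**What the plan says.** Section 11.1 describes the endpoint as a quantity: "The primary endpoint is the change in saturated fat intake in participants allocated to the four different experimental conditions". Section 11.2 then fixes the analysis as a logistic regression on a yes/no outcome: "The effect of the design factors will be determined by comparing the proportion of subjects who have reduced their saturated fat intake". Section 11.3 agrees, assessing the primary endpoint by "calculating the proportion of subjects who reduced that intake within each of the four treatment groups and comparing these proportions". None of these sections states how large a fall must be to count. The continuous analysis is left open: "Further analysis on the actual mean level of reduction may also be carried out".

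The sample size in section 11.3 uses a two-sided 0.05 level and power 0.8, "assuming that the lower proportion is around 10% of subjects". It gives no source for that rate. Its two claims are:
- "A sample size of 200 subjects per cell will allow a difference in proportions of correct responses of approximately 0.08" (10% v 18%)
- "A sample size of 100 subjects per cell will allow a difference in proportions of correct responses of approximately 0.12" (10% v 22%)

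Section 5.2 names the main instrument as a 63-item food frequency questionnaire (FFQ) on a 6-point scale and says of it: "The scale has good test-retest reliability", with r = .61. It lists a two-item self-perception measure under the primary outcome as well.

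**The concern.** A yes/no outcome with no minimum fall treats a trivial drop and a large drop alike, and a trivial rise as failure. Information collected at both visits is thrown away, while the analysis that would use it is optional and has no power statement.

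The planning rate also looks out of line with the outcome. A questionnaire score moves up or down between two occasions even when diet does not change. If any fall counts as a reduction, many controls will be counted by chance, far more than 10%.

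At stake are the power of the primary test, whether the sample-size statement can be relied on, and the meaning of a headline percentage that would contain many subjects whose score fell only through measurement variation.

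**Working it through.** **1. The plan's own figures.** Inputs from section 11.3: lower proportion 0.10, differences 0.08 (n = 200 per group) and 0.12 (n = 100 per group), two-sided 0.05, power 0.80. The standard two-proportion test (pooled variance under the null, separate variances under the alternative) gives:

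| Comparison | Power at stated n | n per group for 80% | Difference with 80% power |
|---|---|---|---|
| 10% v 18%, n = 200 | 0.636 | 295 | 0.100 |
| 10% v 22%, n = 100 | 0.640 | 146 | 0.150 |

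Other formulas do not rescue the claim. For the two comparisons, the required n per group is 292 and 143 (unpooled), 290 and 142 (arcsine), and 319 and 162 (continuity correction). Even a one-sided test gives only 0.747 and 0.751 power. The stated differences come back only if the variance at 10% is used in both arms: (1.96 + 0.84) × √(2 × 0.1 × 0.9 / n) = 0.084 for n = 200 and 0.119 for n = 100. This step needs no assumption about noise, drift or threshold.

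**2. What a cut at zero costs.** For a normal change score cut where a proportion p counts as reduced, the information kept relative to the mean is φ(z_p)² / [p(1 − p)].
- p = 0.5: 2/π = 0.637, so 36% is lost.
- p = 0.4: 0.622.
- p = 0.3: 0.576.
- p = 0.1: 0.342, so 66% is lost.

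In power terms, with 200 per group a mean shift of 2.80 × √(2/200) = 0.280 SD of change has 80% power. As a proportion it is 50% v 61.0%, with power 0.60. With 100 per group the shift is 0.396 SD, or 50% v 65.4%, again with power 0.60.

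**3. Gain from baseline adjustment.** Assume the Time 1-Time 3 correlation is 0.61, the reliability in section 5.2, and measure in FFQ SD.
- Variance of change: 2(1 − 0.61) = 0.78.
- Residual variance of Time 3 given Time 1: 1 − 0.61² = 0.628.
- Information kept by an unadjusted binary analysis relative to the adjusted linear model: 0.637 × 0.628 / 0.78 = 0.51 (0.48 to 0.54 for r from 0.5 to 0.7).
- If the Time 1 score also enters the binary model, this rises to about 0.59.
- Detectable difference at 80% power in the adjusted linear model: 2.80 × √(2 × 0.628 / n) = 0.22 SD for 200 v 200 and 0.31 SD for 100 v 100.
- The 0.22 SD effect is 0.222 / 0.883 = 0.251 SD of change, or 50% v 59.9%. Power is 0.51 as an unadjusted proportion and about 0.57 if baseline is in the binary model.

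**4. Plausibility of 10%.** With symmetric change, no drift and few ties, half of controls fall below their own baseline. Mean drift in controls of 0.2 FFQ SD either way gives 41% to 59%, and 0.3 SD gives 37% to 63%. Ties matter little for the FFQ: a simulated 63-item, 6-point sum score with retest correlation near 0.6 gave 49.7% reduced and 1% tied. For a two-item, 7-point measure it gave about 42% reduced and 16% tied. To reach 10% by drift, control intake would have to rise by 1.2816 × 0.883 = 1.13 FFQ SD.

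**5. Section 11.3 at other base rates.** The differences detectable at 80% power are:

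| Base rate | n = 200 per group | n = 100 per group |
|---|---|---|
| 10% | 0.100 | 0.150 |
| 30% | 0.135 | 0.193 |
| 40% | 0.139 | 0.197 |
| 50% | 0.138 | 0.193 |

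At 40-50%, power for differences of exactly 0.08 and 0.12 is about 36% and 40%.

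**The case against.** **The 36% and 40% figures.** A reader might infer that true power is about half of what is claimed. The documents do not support that as a general statement, because the figures hold only if the effect stays fixed as a risk difference while the base rate moves. If the shift in the underlying change is held fixed instead, 10% v 18% (0.366 SD of change) becomes 50% v 64.3% with power 0.83 at 200 per group, and 10% v 22% (0.509 SD) becomes 50% v 69.5% with power 0.81 at 100 per group. At a constant odds ratio, the scale of the planned logistic model, power is 0.92 and 0.89. The protocol does not say on which scale the effect is constant.

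**The reliability figure.** It is tempting to say that r = .61 contradicts the 10% rate. It does not: a share near one half follows from symmetry, little drift and no threshold, and any correlation below 1 gives it. The value of r matters only for how much drift would be needed and for the gain from baseline adjustment. Its use as the Time 1-Time 3 correlation is an assumption.

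**A threshold set later.** Section 11.2 defers to a full statistical analysis plan, which could define a minimum fall. That stands, and it could make 10% attainable. It would not answer the loss of information, which grows to about 66% at a 10% rate.

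**The 51% figure.** It sets a binary analysis without baseline against a linear one with it. Section 11.2 admits covariates significant at 0.05 and mentions intake history if groups differ, so baseline might enter the logistic model. The loss is then smaller but remains.

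**Internal conflict.** Sections 11.1 and 11.2 might be read as contradictory. Section 11.3 says how the endpoint is assessed, so the plan is coherent on this; the choice is inefficient rather than inconsistent.

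**Conclusion.** The point holds in two parts.

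First, and without added assumptions, the differences stated in section 11.3 have about 64% power at the plan's own 10% rate; 80% power needs about 0.10 and 0.15.

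Second, the yes/no analysis is a poor use of the data. For an approximately normal change score it loses about 36% of the information at a cut at zero, taking 80% power down to about 60%. It loses more against a baseline-adjusted model, by an amount that depends on the Time 1-Time 3 correlation and on whether baseline enters the logistic model. Marked non-normality, which section 11.2 itself allows for, would change these percentages.

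The 10% rate is unsourced, and it is implausible if any fall counts and control change is roughly symmetric with little drift. That is a conditional statement, not a figure in the protocol. How the base rate alters power depends on the scale on which the effect is held constant.

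**What to change.** Make the primary analysis a linear model of the Time 3 FFQ saturated-fat score on the two design factors, their interaction, the Time 1 score, age group and gender. Report mean differences with 95% confidence intervals. Keep the proportion reduced as a secondary summary, with the size of fall that counts stated.

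Restate section 11.3 in SD units: about 0.22 SD for 200 v 200 and 0.31 SD for 100 v 100, with the assumed correlation of 0.61 made explicit. If the proportion stays primary, correct the detectable differences (0.10 and 0.15 at a 10% rate), show them across base rates of 10% to 50%, give a basis for the rate chosen, and say on which scale the effect is assumed.

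The cost is protocol wording and a recalculation, with no new visits or measurements. The downsides are that the headline result is in score units rather than a percentage, and that a transformation, already foreseen in section 11.2, may be needed.

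### Section 11.2 lets the trial data choose the primary model's covariates and does not fix baseline saturated fat intake as one of them

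*Protocol*

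**What the plan says.** Section 11.1 bases the comparison on change: efficacy is judged "via the change in saturated fat intake between the baseline and final diet assessments", with randomisation "stratifying for age group (30-45 years or 46-60 years) and gender".

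Section 11.2 analyses the proportion of subjects who reduced their intake, "using a logistic regression model which includes the two design factors and their interaction". An analysis of mean reduction is optional, "using an analysis of variance model including the design factors and their interaction". Two rules then govern covariates:

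- **Significance rule:** "The stratification variables will be included in the models as will other covariates found significant at the 0.05 level". The protocol lists no candidates and does not say in which model significance is judged.
- **Imbalance rule:** "If there are any relevant differences at baseline measurements between the four groups, we will adjust the outcome of these factors". The examples are "e.g. diet knowledge, history of saturated fat intake, socio-economic status". No threshold for a relevant difference is given.

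The assessment table in section 5.2 schedules the food-frequency questionnaire (FFQ) at Time 1 and Time 3, so every completer should have a baseline score.

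**The concern.** Both rules let the observed data decide what the primary model contains. The imbalance rule also asks the wrong question. Under randomisation, baseline differences are chance, and their size says nothing about whether a covariate predicts the outcome, which is what makes adjustment worthwhile.

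Baseline intake does predict the outcome. Change is computed from it, so subjects with a high first score tend to fall and those with a low one tend to rise. If baseline is left out, power is lost, and a chance imbalance just short of relevant stays in the treatment contrast. In a logistic model the odds ratio also changes meaning with each covariate added (non-collapsibility), so the quantity estimated is not known until the data have been seen.

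**Working it through.** **Inputs.** Two-sided alpha 0.05, power 0.8, lower proportion 10%, 200 subjects per factor level (section 11.3). FFQ test-retest r = 0.61 (section 5.2). Using 0.61 as the trial's baseline-to-follow-up correlation is an assumption, so a range of 0.4 to 0.8 is shown.

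**The plan's own figures.** None is given for covariate adjustment. Section 11.3 claims a difference of about 0.08 from 10% with 200 per level, "to be detected at a two-sided 0.05 significance level with power of 0.8". That does not reproduce: 10% v 18% has 63.6% power, and the difference detectable with 80% power is about 0.100. This is a separate point, but it is why 10% v 19.8% is used below as the case with about 80% power. Because section 11.2 sets no minimum size of reduction, a responder rate near 50% is also shown (50% v 64%).

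**Step 1: baseline predicts change.** With equal variances of 1 at both times, corr(baseline, change) = −√((1−r)/2) = −√(0.39/2) = −0.442.

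**Step 2: planned logistic analysis.** The model was simulated with 400 subjects, both factors, their interaction and the strata, using 3,000 to 4,000 runs per case. *Relevant* was read as p<0.05 in a four-group F-test. The table gives power for the Heart-Age factor.

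| r | Case | No baseline | Imbalance rule | p<0.05 rule | Always adjusted | Gain, always v none |
|---|---|---|---|---|---|---|
| 0.4 | 10% v 19.8% | 78.9% | 79.3% | 85.0% | 85.0% | 6.1 |
| 0.61 | 10% v 19.8% | 79.5% | 79.9% | 82.9% | 82.9% | 3.3 |
| 0.8 | 10% v 19.8% | 78.9% | 79.0% | 80.7% | 80.8% | 1.9 |
| 0.4 | 50% v 64% | 80.7% | 81.7% | 88.6% | 88.6% | 7.9 |
| 0.61 | 50% v 64% | 80.8% | 81.1% | 86.3% | 86.3% | 5.6 |
| 0.8 | 50% v 64% | 79.5% | 79.9% | 82.5% | 82.5% | 2.9 |

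Read this way, the imbalance rule admits baseline in about 5% of trials, so it gives almost none of the gain. The p<0.05 rule, if baseline is a candidate, admits it in 97% to 100% of trials and gives nearly all of it.

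**Step 3: optional analysis of mean change.** The residual variance is 2(1−r) = 0.78 for the change score and 1−r² = 0.628 after adjustment. The ratio is (1+r)/2 = 0.805, a cut of 19.5% (30% at r = 0.4, 10% at r = 0.8). Adjusted, 400 subjects do the work of 400/0.805 = 497. An effect with 80% power adjusted has Φ(2.80×√0.805 − 1.96) = 71% unadjusted.

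**Step 4: conditional type I error without baseline adjustment.** Suppose two factor levels differ at baseline by 1.9 SE. The unadjusted statistic then has mean 1.9k and SD √(1−k²), where k is the absolute correlation of the outcome with baseline.

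- Mean change: k = 0.442, mean 0.839, SD 0.897; P(|T|>1.96) = 10.7% (9.4% to 12.2% for r = 0.7 to 0.5).
- Binary, 10% responders: k = (0.1755/0.3)×0.442 = 0.258, mean 0.491, SD 0.966; 7.0%.
- Binary, 50% responders: k = (0.3989/0.5)×0.442 = 0.352, mean 0.669, SD 0.936; 8.6%.

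**Step 5: overall type I error.** In the null simulations (Monte Carlo SE about 0.35 points) the imbalance rule gave 4.4% to 5.7% and the p<0.05 rule 4.8% to 6.1%. The 6.1% arose where baseline entered in every trial, and prespecified adjustment gave the same figure there, so selection added nothing. Reporting whichever of the adjusted and unadjusted models has the smaller p-value gave 6.2% to 7.9%.

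**The case against.** **Baseline may enter anyway.** A reader might infer that baseline intake is adjusted for only when the groups happen to differ, so that power is lost in most realisations of the trial. The text does not support *only*. The significance rule has no candidate list and does not exclude baseline intake, and a variable this predictive would nearly always pass it. On that reading the power loss almost vanishes, and an imbalance short of relevant would also be corrected. This stands.

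**The largest figures belong to the optional analysis.** The 19.5%, the 497 and the 10.7% describe mean change, which the protocol says may be analysed. The trial is planned and sized on the proportion who reduced intake, where the effects are smaller. *Precision gain* is not literally true of the primary model either: adjustment raises power, but the standard error of the conditional odds ratio does not shrink. This stands too.

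**The conditional error is a chosen case.** It fixes the imbalance at 1.9 SE and assumes that this is not judged relevant. The protocol sets no threshold, and an analyst might adjust. It illustrates the mechanism and is not an expected error rate.

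**The statistical analysis plan may settle the details.** A candidate list and a definition of relevant are normal content for that plan, and their absence here is no defect in itself. But section 11.2 commits to both data-dependent rules, and a plan that follows the protocol inherits them. This answers the objection only in part.

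**Conclusion.** The point holds as a failure of prespecification with a modest cost in power. Section 11.2 lets the data select the primary model and leaves baseline intake, the strongest predictor that can be expected in advance, without a fixed place or a clear governing rule.

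- **Primary logistic analysis:** always adjusting gains about 3 to 6 points of power at r = 0.61 (2 to 8 over r = 0.4 to 0.8) against no adjustment or the imbalance rule, and almost nothing if baseline would enter at p<0.05.
- **Optional mean change:** variance falls by about 19.5% (10% to 30% over r = 0.8 to 0.4).
- **Unadjusted, with a 1.9 SE imbalance:** conditional type I error is about 7% to 9% for the binary endpoint and 10.7% for mean change.

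A reader might also infer that the rules inflate the overall false-positive rate. Applied mechanically, they do not to any material extent. The risk comes from the freedom to decide what is relevant, which covariates are candidates and which model to report, and from an odds ratio whose meaning shifts with that decision.

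The figures assume that a test-retest reliability stands in for the trial correlation, that variances are equal at both times, and that history of saturated fat intake means the baseline measure. The imbalance-rule results also assume that *relevant* means a significant F-test.

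**What to change.** In section 11.2, replace both covariate sentences with one fixed set for every primary model: Time 1 FFQ score, age group and gender, entered whatever their p-values or baseline balance. Delete the p<0.05 rule and the baseline-difference rule. Label any other adjustment, such as diet knowledge or socio-economic status, as sensitivity analysis. Use the same set if mean change is analysed.

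The cost is two sentences and one model degree of freedom, with no new data collection. There are two small downsides: the primary odds ratio becomes conditional on baseline intake and should be described as such, and the other baseline factors leave the primary model.
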